## Abstract

**Background:**

Peripheral neuropathy (PN), including numbness, loss of sensation, paresthesia, a burning sensation, and stabbing pain in extremities, is a common complication in people with human immunodeficiency virus (PHIV). Medications commonly used to treat HIV-related PN are not effective and lead to many side effects. HIV-related PN symptoms may be alleviated or treated with a series of therapeutic Chinese foot massages (TCFM), which are non-invasive and relatively safe. However, relevant studies are lacking.

**Study design:**

This proposed trial is a prospective, two-arm, parallel, double-blinded, randomized controlled trial.

**Aim:**

This proposed trial aims to assess the effectiveness of TCFM on HIV-related PN in people with HIV (PHIV).

**Outcomes:**

The primary outcomes, measured at baseline, end of TCFM/placebo, and twelve weeks after, include (1), lower extremity pain, (2) lower extremity functioning, and (3) health-related quality of life. The secondary outcomes, measured throughout the trial process, include (1) recruitment and completion rate (No. of referred, No. of eligible, No. of enrolled, No. of withdrawals, trial recruitment rate, and trial completion rate), (2) participants' safety (No. and severity of adverse events), (3) treatment adherence (average time of each message session, No. of completed sessions, and No. of missed sessions), and (4) compliance (No. of participants completing the trial following the initial group assignment).

**Sample size:**

An estimated 142 participants in total, or 71 participants in each arm, will be needed for this trial.

**Trial status:**

This trial was registered at ClinicalTrials.gov of the National Institute of Health on Oct 26, 2022 (ClinicalTrials.gov Identifier: NCT05596123). The researchers expect to recruit participants starting in Feb. 2023 and ending in Feb 2025.

## Introduction

More than a million people in the US are infected with the human immunodeficiency virus (HIV). They may suffer from progressive immune system failure and its complications over time due to the retrovirus (1). People with human immunodeficiency virus (PHIV) are nowadays living longer because of the development of antiretroviral therapy (ART) and interventions to increase medication adherence over the years (2, 3). Young PHIV in the US can expect to live into their early 70s with an increased life expectancy of 14.7 years between 2000–2002 and 2006–2007, which is very close to the average lifespan of the general population (4–6). As a result, HIV in the US has gradually evolved from an infectious disease to a chronic condition requiring ongoing self-care and symptom management for a lifetime. PHIV are more likely to experience the neurotoxic side effects of ART due to their potentially longer exposure to ATR with an increased life span (7).

Peripheral neuropathy (PN), the most prevalent neurological symptom in this population, affects about 30–67% of people with PHIV. Although common, PN is often overlooked and misdiagnosed in PHIV (8). HIV-related PN is associated with neurotoxic effects of ART and HIV virus (8, 9). Numbness, loss of sensation, most often in the toes and soles, paresthesia, a burning sensation, and stabbing pain are the major symptoms of HIV-related PN, which most commonly affects feet and less frequently hands (10, 11). There are six and more types of HIV-related PN (8). The type of ART that PHIV use, the stage of their HIV infection, their immune function, and the presence of additional infections affect the type and severity of HIV-related PN symptoms (8, 12). PN compromised PHIV's quality of life (13). However, there is no currently available treatment for HIV-related PN that has been approved by the U.S. Food and Drug Administration. Many PHIV endure PN without using any interventions or medications. For symptom management, some PHIV either no longer take the associated medications or use off-label analgesics, antidepressants, or anti-seizure medications. These medications may cause side effects, including nausea, vomiting, dizziness, and fatigue, which are very common and further disrupt PHIV patients' daily lives. Moreover, these medications only partially alleviate PN symptoms (14). Unfortunately, pharmacological interventions to relieve HIV-related PN are rarely evaluated in research. To our best knowledge, in published studies, only topical capsaicin, smoked medical marijuana, and recombinant human nerve growth factor outperformed placebo in treating HIV-related sensory neuropathy pain (11). To treat PN in PHIV, a combination of pharmacological and nonpharmacological approaches is desired (15). Unfortunately, nonpharmacological interventions on HIV-related PN, however, were the subject of very few existing studies. To our knowledge, only hypnosis (16), spinal cord stimulation (17), lower extremity splinting (18), vibratory stimulus (19), progressive-resisted exercises (20), cognitive behavior therapy (21), and acupuncture/moxibustion (22) have been examined by randomized control trial with the purpose of alleviating HIV-related PN. All the above studies were subject to small sample sizes and methodological limitations. Moreover, only the acupuncture/moxibustion study of the above-mentioned studies demonstrated marginally significant pain reduction compared to the placebos (20). Therefore, non-pharmacological inventions are urgently needed to explore the treatment of HIV-related PN.

Tui Na or therapeutic Chinese massage (TCM) has been used as a therapy in China for more than 5,000 years to 1600–1000 BC (23, 24). Early in TCM history, the technique was described as AnMo (massage) and Dao Yin (physical and breathing exercises), but in current times involves the systematic manual palpation, push-pull, and stroking of acupoints, soft tissues, and muscles by the fingers, hands, elbow, knee, or feet of a therapist (25). Pressure on the foot's and lower leg's muscles and joints will stimulate the somatosensory system by stimulating several receptors and increasing blood flow in the associated areas (26). TCM may assist in removing energy blocks along particular meridians linked to particular diseases or symptoms (24). TCM has been used to alleviate chronic low back pain and neck pain (27, 28), help manage cervical radiculopathy (29), and control hypertension and diabetes (25, 30). A study has found that participants of high-intensity cyclic exercise who also received TCM were significantly more physically fit, better exercise performance, more balanced body composition, and improved physical and mental health (31). Additionally, few adverse events occur when this non-invasive treatment is s if performed by trained professionals (32).

Previous studies with small sample sizes and methodological limitations have provided some evidence that massage could improve PN caused by diabetes (26, 33). To the best of our knowledge, no study has examined the effectiveness of TCM on HIV-related PN. Thus, the aim of this proposed trial to propose a randomized controlled trial that aims to (1) investigate whether a series of 25-min sessions of TCFM (tui na) given six times a week, in comparison to a placebo massage, could help PHIV with lower extremity PN symptoms feel better and function better and (2) evaluate recruitment rate, completion rate, participant safety, treatment adherence, and treatment compliance of such trial.

## Materials and methods

### Ethical approval

The University of Houston-Downtown Committee for the Protection of Human Subjects approved the proposed trial of this protocol after conducting an ethical review. Prior to being enrolled in the trial, participants will be fully informed regarding the possible risks involved, the informed consent process, confidentiality, and secure data storage. Participants will be informed that although TCM is generally safe, mild discomfort, soreness, and slight bruising may appear at or after a session. Severe but very rare adverse events include disc herniation, soft tissue trauma, neurologic compromise, spinal cord injury, vertebral artery dissection, bone fracture, hematoma or hemorrhagic cyst, syncope, cauda equina syndrome, pain, and dislocation (32). Participants will be informed that their decision of whether to participate in this trial will not affect any health or education service they receive at present or in the future. Participants will be guaranteed that they can leave the trial at any time without providing a reason or leading to any consequences. Oral and written informed consent will be obtained from every participant. This trial was registered with ClinicalTrials.gov of the National Institute of Health on Oct 26, 2022 (ClinicalTrials.gov No: NCT05596123).

### Trial design

This proposed trial is a prospective, double-arm, parallel, double-blinded, randomized controlled trial. Participants, the outcome assessors, and the statistician will be unaware of the group assignment. A one-to-one ratio will help randomly assign participants to the TCFM group or the placebo massage group evenly. Six weekly 25-min TCFM sessions will be delivered to participants in the TCFM group. Six weekly 25-min placebo massage sessions will be delivered to participants in the placebo massage group. Depending on the convenience and preference of participants, the TCFM or placebo massage will be conducted either at participants' homes or in a room provided by University of Houston-Downtown. The trial will be reported following the Consolidated Standards of Reporting Trials (CONSORT) Statement (34). Figure 1 shows the enrolment, interventions, and assessment schedule of this proposed trial.

**Figure 1 F1:**
[figure not shown]
The flow chart of the study.

### Study population and eligibility criteria

Participants' inclusion criteria are those who (1) have confirmed HIV diagnosis based on providers' verification with participants' approval; (2) self-report PN-related symptoms in their lower extremity, including sharp, jabbing, throbbing, or burning pain, numbness, decreased sensation to pinprick, prickling or tingling feeling, lack of coordination and falling muscle weakness, and extreme sensitivity to touch (35); (3) are not taking any medications, including pain medicine, to alleviate PN; (4) age 18 years and older; (5) can communicate with researchers in English or Mandarin Chinese; (6) are not pregnant or lactating; (7) are not enrolled in other clinical trials. People who have received non-pharmacological interventions, including any type of massage, to treat their PN symptoms in the past 6 months will be ineligible for participation.

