### Recruitment

Two interventionists will be trained by the principal investigator on the recruitment protocol of this trial prior to the beginning of the trial. Flyers, officers' recommendations, sharing posts on Facebook, and the snowball method will be used to recruit PHIV from healthcare facilities at the Texas Medical Center in the US. People interested in the trial are encouraged to get in touch with the PI by phone or email to see if they qualify. Every interested respondent will have a phone or zoom conversation with the PI or the interventionists as an initial screening. The PI or the interventionists will inquire as to whether they experience any of PN symptoms in their lower extremity, such as numbness, decreased sensation to pinprick, prickling or tingling, lack of coordination and falling, muscle weakness, and extreme sensitivity to touch. If they exhibit PN symptoms in their lower extremity, the PI or the interventionists will schedule a time to meet them face-to-face at their home or a room provided by the University of Houston-Downtown, depending on their preferences and convenience. The PI or the interventionists will conduct a complete screening of the person against the inclusion and exclusion criteria when they meet in person, determine whether they are eligible for participation, and obtain informed consent if they are eligible and willing to participate in the trial. The PI, the interventionists, the outcome assessors, and the therapists will all wear facial masks throughout the trial to protect every person they meet.

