### The TCFM (Tui Na)

Participants in the TCFM group will receive 6 weekly 25-min TCFM sessions provided by a therapist. The therapist will begin each session with an assessment of the legs and toes of the affected extremity for broken skin and lesions that would identify areas at risk for irritation during the massage and need to be avoided. The participant will be positioned with support to their foot and legs, with the sole of the foot plantar flexed and the therapist directly in alignment with the foot. The therapist will serially perform the following four steps for each TCFM session.

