#### Step two: Stimulating the AhShi, along with breaking up and dispersion of stagnations

During the finger-pressing massage, the therapist will identify any sensitive areas, trigger points, contracted muscle areas, and nodules. As those areas are identified during one finger-pressing procedure, additional time will be spent to elicit a therapeutic response of change in sensation. The AhShi points will be treated with deeper penetrating pressure to surrounding the dragon (a local treatment using intense energy around the affected area) using vibration. The stagnation will be further dispersed with consistent pressure to the center of AhShi with the whorled surface of the thumb.

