The secondary outcomes include (1) recruitment and completion rate (No. of referred, No. of eligible, No. of enrolled, No. of withdrawals, trial recruitment rate, and trial completion rate), (2) participant safety (No. and severity of adverse events), (3) treatment adherence (average time of each message session, No. of completed sessions, and No. of missed sessions) and compliance (No. of participants completing the trial following the initial group assignment). Adverse events will be recorded by the therapists in the notes. A published systematic review of the negative effects of massage therapy in the context of pain found the following adverse but rare events which the therapists will be instructed to watch out for, including disc herniation, soft tissue trauma, neurologic compromise, spinal cord injury, vertebral artery dissection, bone fracture, hematoma or hemorrhagic cyst, syncope, cauda equina syndrome, pain, and dislocation (32).

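### The entry criteria exclude no condition that raises the risk of the local massage harms the protocol names, and the stated checks begin only after randomisation

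*Protocol article*

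**What the plan says.** **Who may enter.** The section Study population and eligibility criteria sets out seven numbered criteria: HIV diagnosis, self-reported lower-limb neuropathy symptoms, no medication for the neuropathy, adult age, language, and finally "6) are not pregnant or lactating; (7) are not enrolled in other clinical trials". One further rule bars anyone who had non-drug treatment for neuropathy in the past 6 months. The qualifying symptoms include "numbness, decreased sensation to pinprick, prickling or tingling feeling, lack of coordination and falling muscle weakness".

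**How entry is checked.** Under Recruitment, staff "conduct a complete screening of the person against the inclusion and exclusion criteria when they meet in person". No other medical check before randomisation is described. The health and lifestyle items collected at the first visit are alcohol, smoking, body mass index and depressive symptoms.

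**Which harms are named.** Under Ethical approval, participants are told that "Severe but very rare adverse events include disc herniation, soft tissue trauma" and, further along the same list, "bone fracture, hematoma or hemorrhagic cyst, syncope, cauda equina syndrome, pain, and dislocation". The paragraph on secondary outcomes tells therapists to watch for the same events and gives the source as "A published systematic review of the negative effects of massage therapy in the context of pain".

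**What is done to the foot.** In step two of the active massage, "The AhShi points will be treated with deeper penetrating pressure". Step four adds shaking and rotation of the ankle, and rotation and pulling of the toes.

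**Which safeguards exist.** Under The TCFM (Tui Na), "The therapist will begin each session with an assessment of the legs and toes of the affected extremity for broken skin and lesions". The Safety section adds inspection for indurations or damage, avoidance of broken skin, monitoring of responses, and gentler massage if the participant complains of increasing pain. The therapists are certified, have more than 2 years of experience, and are trained and examined on the protocol.

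**The concern.** The protocol names injuries that firm pressure and joint manipulation could cause at the foot and ankle, then asks nobody at entry whether they are prone to them. As written, a person with a bleeding disorder or a recent leg fracture is eligible and can be allocated to the active massage. The medication criterion does not help, because it concerns only drugs taken for the neuropathy. An anticoagulant user passes it.

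The safeguards at the sessions leave two gaps. Skin inspection does not reveal a bleeding disorder, anticoagulation or fragile bone. Easing off on a complaint of pain works less well in someone enrolled because the foot is numb.

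What is at stake is participant safety. The primary comparison is not affected.

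**Working it through.** **1. The plan's own figure.** The exposure below uses the 71 per arm in Sample size, so I checked it first. The MMRM formula is n per arm = 2 × φ × (z₀.₉₇₅ + z₀.₈₀)² × SD² / δ². Under compound symmetry with correlation 0.8, full baseline data and 75% retained afterwards, φ = 0.8² + (1 − 0.8²)/0.75 = 0.64 + 0.48 = 1.12. With SD 2 and difference 1, n = 2 × 1.12 × 7.849 × 4 = 70.33, rounded up to 71. The figure reproduces. The concern does not depend on it beyond the head count.

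**2. Criteria set against the named harms.**

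| Named harm | Risk factor one would screen for | Covered by the 7 criteria or the added rule? |
|---|---|---|
| Haematoma | bleeding disorder, anticoagulant use | no |
| Fracture | bone fragility, recent fracture | no |
| Dislocation | unstable ankle or foot joint | no |
| Soft-tissue trauma | extensive wounds or ulcers, recent injury | no |

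The count is 0 of 7 criteria and 0 of 1 added rule. Pregnancy is excluded but is not evidently a risk factor for any of the four. The middle column is clinical judgement and is not taken from the protocol.

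**3. When each safeguard acts.** Risk disclosure comes before enrolment but screens nobody out. Skin inspection, avoidance of broken skin, monitoring and gentler massage are all carried out by the therapist at sessions, after consent, baseline and randomisation. The skin check does come before contact. The only explicit trigger for reducing force is a complaint of pain.

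**4. Exposure.** Planned active-arm exposure is 71 × 6 = 426 sessions. This is a ceiling that assumes full attendance, whereas Sample size allows 25% dropout at post-baseline visits.

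**5. How many at-risk people could be enrolled.** The documents give no prevalence, so a share p of otherwise eligible people is assumed.

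| Assumed p | Expected people, 71p | Expected sessions, 426p | Chance of at least one, 1 − (1 − p)⁷¹ |
|---|---|---|---|
| 2% | 1.4 | 8.5 | 76% |
| 5% | 3.6 | 21 | 97% |
| 10% | 7.1 | 43 | 99.9% |

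**6. Recruitment cost of excluding them.** Otherwise eligible people needed to fill 142 places = 142/(1 − p). This gives 144.9, 149.5 and 157.8, or 145, 150 and 158 when rounded up: 3, 8 and 16 more than 142.

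**The case against.** The strongest objection is that this is an omission from a condensed article, and a fuller protocol may hold more exclusions. That would carry weight if the article pointed to further criteria. It does not. It gives a numbered list, makes that list the operative screening test, and says in the Discussion that the methodology is detailed enough to reproduce. A stated eligibility rule that is too loose can fairly be criticised.

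Several other points stand in part:

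- The harms come from a review of massage for pain in general, are called very rare, and include spinal and neck injuries irrelevant to a foot massage. What the protocol expects of this massage is mild discomfort, soreness and slight bruising. This holds and keeps the absolute risk low.
- Treating four of the harms as plausible at the foot, and choosing the risk factors, is clinical judgement. This holds too, although it fits the techniques described.
- Consent discloses the harms beforehand, and an at-risk person could decline or speak up. That is some protection, but weaker than being asked.
- The Safety section reaches beyond pain and broken skin, and lets therapists adapt treatment. The entry list also admits people with pain and extreme sensitivity to touch, in whom feedback would be good. So the reliance on pain report is partial.
- The chance of enrolling at least one at-risk person follows mechanically from an assumed prevalence and says nothing about how many would be hurt. This is correct.
- That falling is an entry symptom makes recent leg injury plausible, but the documents contain no injury data.

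**Conclusion.** The concern holds. None of the seven criteria or the added rule addresses a risk factor for haematoma, soft-tissue trauma, fracture or dislocation, and the session checks cannot detect the less visible ones. If 2% to 10% of otherwise eligible people had such a condition, the active arm would expect about 1.4 to 7.1 of them among 71. That share is an assumption, and the number who would be harmed cannot be estimated from the documents. This is a gap in participant protection with low absolute risk. It contradicts nothing in the protocol and has no claimed bearing on the primary analysis. It should be corrected because the remedy is cheap. Confidence is medium, since the link from each condition to each harm rests on clinical judgement.

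**What to change.** Add to Study population and eligibility criteria exclusions for:

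- a bleeding disorder or anticoagulant use;
- a recent lower-limb fracture, or an unstable ankle or foot joint;
- known bone fragility;
- open wounds or ulcers on the foot or leg too extensive to avoid.

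The trial's clinicians should confirm the wording and time windows. Ask about these conditions at the face-to-face screening described under Recruitment, and do the first foot and skin inspection there, before randomisation. Keep the checks at each session as they are.

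The cost is an eligibility amendment, a few questions and a foot inspection at a visit the trial already holds, with no extra staff. Generalisability narrows slightly. Under the 2% to 10% assumption, filling 142 places needs 145 to 158 otherwise eligible people, which is 3 to 16 more.

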### Recruitment

Two interventionists will be trained by the principal investigator on the recruitment protocol of this trial prior to the beginning of the trial. Flyers, officers' recommendations, sharing posts on Facebook, and the snowball method will be used to recruit PHIV from healthcare facilities at the Texas Medical Center in the US. People interested in the trial are encouraged to get in touch with the PI by phone or email to see if they qualify. Every interested respondent will have a phone or zoom conversation with the PI or the interventionists as an initial screening. The PI or the interventionists will inquire as to whether they experience any of PN symptoms in their lower extremity, such as numbness, decreased sensation to pinprick, prickling or tingling, lack of coordination and falling, muscle weakness, and extreme sensitivity to touch. If they exhibit PN symptoms in their lower extremity, the PI or the interventionists will schedule a time to meet them face-to-face at their home or a room provided by the University of Houston-Downtown, depending on their preferences and convenience. The PI or the interventionists will conduct a complete screening of the person against the inclusion and exclusion criteria when they meet in person, determine whether they are eligible for participation, and obtain informed consent if they are eligible and willing to participate in the trial. The PI, the interventionists, the outcome assessors, and the therapists will all wear facial masks throughout the trial to protect every person they meet.

